**Influence of cardiopulmonary bypass pump on selenium status of cardiac surgical patients, undergoing coronary artery bypass surgery.**

*Inclusion criteria:*

100 patients, undergoing open heart surgery should be included in the trial. Here, 50 patients will be operated conventional, with the use of CPB and cardioplegia. Further 50 patients will be operated on the beating heart, without the use of CPB (OPCAB= „off pump coronary artery bypass“). The surgeon ([name]) will perform the surgery in all patients.

Included will be all patients suffering from a coronary 3-vessels heart disease. They will undergo surgery in general anaesthesia with median sternotomia in the case of elective or urgent indication for treatment. Patients should be free of further serious cardiac diagnoses (valve-disease, aneurysms etc.). Excluded are patients with ischemic cardiomyopathy. The aimed revascularization should be completely performed and conducted by one surgeon. 50 patients are undergoing conventional surgery, with the use of cardiopulmonary bypass (CPB), with moderate hypothermia and cardioplegic cardiac arrest. The other 50 patients will be treated without the use of CPB (OPCAB).

Only adults, after written informed consent for the study participation will be included.

*Exclusion criteria:*

Excluded will be patients with emergency surgery (NSTEMI or STEMI), patients with ischemic cardiomyopathy or additional cardiac diagnoses (valve-diseases or aneurysms), patients incapable of giving consent, pregnant patients and women with childbearing potential, in which pregnancy cannot be excluded.

Patients will be enrolled in the clinical trial, after patient information, at least, the evening before the operation.

*Methodology of study:*

After induction of anaesthesia, within one hour after admission the patient to the intensive care unit and every further morning on the intensive care unit or intermediate care unit (IMC), 10 ml blood will be drawn from the central venous line, placed independently of the study for the operation. A separately puncture for this purpose it is not necessary.

Selenium values will be measured from this blood in the whole blood sample by electrothermal atomic absorption spectroscopy.

Beside this, the following parameters will be measured daily in the routinely diagnostic and later correlated with the selenium concentration at the respective time points. The measurement of glutathione peroxidase (GPX) und thioredoxin (TRX) reductase will be conducted in the laboratory of the company Biosyn. The „macrophage migration inhibitory factor (MIF)“ will be determinated from the remaining blood.

*Determinated parameters:*

- Procalcitonin
- CRP
- IL-6, IL-10
- Leukozyten
- Glutathione peroxidase (GPX)
- Asymmetric dimethylarginin (ADMA)
- Thioredoxin reductase (TRX)
- Platelets
- Bilirubin
- Creatinine
- Lactat
- Albumine
- AT-III
- CK, CKMB and troponin
- Duration of mechanical ventilation
- Duration of hospitalisation
- SOFA-Score
- SAPS-Score

All blood samples will be kept until study end and their analysis (max. 24 months) and will be disposed thereafter.

Values of selenium, markers of oxidative stress (GPX, ADMA) and inflammation (IL-6, IL-10) from the 1.POD on will be used for possible long-term analyses of selenium course.

All data will be recorded on a documentation form.

*Study duration:*

The study will be terminated, as 100 patients are included or after a maximum of 24 months.

*Risks:*

Patients are not exposed to additional risk by blood sampling before surgery, after admission to intensive care unit, and every further day on the intensive care unit. All blood samples will be drawn from catheter, placed independently of study participation, for cardiovascular monitoring. Therefore blood sampling for this study is not associated with pain.

Summarized, according to current scientific evidence there is not expected an impairment or additional stress for the participating patients.

*Benefits:*

There is no benefit for the individual participant of the study expected.

Significant low selenium values (lower than the reference value of selenium in whole blood of 100-140µg/L) will be detected.

*Statistic:*

All data will be recorded pseudonymized and analyzed anonymized.

Recorded patient data will be anonymized, by numbering in order of study inclusion. Thereafter the mean and standard deviation of the recorded data will be calculated and this data will be further statistically evaluated.

Hereby the correlation of measured selenium blood values and laboratory chemical parameters of inflammation and the clinical patient outcome will be evaluated. Differences between the groups (OPCAB vs. conventional CPB-surgery) concerning the laboratory chemical and clinical course will be statistically analyzed by tests comparing independent groups. Correlations between the different variables will be analyzed by the methods of Pearson and Spearman-rho. The predictive value of selenium blood levels concerning certain outcome parameters will be determined by the receiver-operating characteristic curves (ROC).

*Quality assurance:*

This observational study will be conducted under the Good Clinical Practice guidelines.

*Adresses and responsibilities:*

Scientific direction:

PD [name]

Senior consultant

Department of Anaesthesiology

University Hospital Aachen

[name]

[name]

Direct line - [contact]

[contact] (secretariat)

[contact]

E-Mail: [contact]

Involved physicians:

[name], Senior consultant, Department of Thoracic, Cardiac and Vascular Surgery

[name] (direct line: [name]), resident physician, Department of Anaesthesiology

Laboratory:

biosyn Arzneimittel GmbH

[name]

[name]

Telefon: [name]

Telefax: [name]

[contact]

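### How patients come to CPB or OPCAB is not stated, and the listed data lack the main pre-operative risk factors, so confounding of the clinical-course comparison can be corrected only in part

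*Protocol*

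**What the plan says.** The Quality assurance section of the protocol gives the design: "This observational study will be conducted under the Good Clinical Practice guidelines". No randomisation is described.

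The Inclusion criteria section sets two quotas: "50 patients will be operated conventional, with the use of CPB and cardioplegia", and "Further 50 patients will be operated on the beating heart, without the use of CPB". One surgeon performs all operations and complete revascularization is the aim. Neither this section nor any other says how a patient comes to one technique or the other.

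On eligibility, the same section states "Included will be all patients suffering from a coronary 3-vessels heart disease", with surgery "in the case of elective or urgent indication for treatment". The Exclusion criteria section narrows this: "Excluded will be patients with emergency surgery (NSTEMI or STEMI), patients with ischemic cardiomyopathy or additional cardiac diagnoses (valve-diseases or aneurysms". Suitability for both techniques is not a criterion.

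Under Determinated parameters the protocol lists laboratory values, "Duration of mechanical ventilation", length of hospital stay, SOFA and SAPS. Age, sex, ejection fraction, diabetes, urgency and a surgical risk score are not on the list. Under Methodology of study, the first blood sample is drawn after induction of anaesthesia, and the Risks section confirms sampling before surgery.

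The Statistic section then makes the group comparison a declared analysis: "Differences between the groups (OPCAB vs. conventional CPB-surgery) concerning the laboratory chemical and clinical course will be statistically analyzed", using two-group tests.

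**The concern.** The title asks about the influence of the bypass pump, so the contrast between the two techniques is central. In a non-randomised study that contrast is interpretable only if the groups are alike at the outset, or if the ways in which they differ are recorded and can be allowed for. Here the route to each technique is unstated, and the variables most likely to influence both the choice of technique and recovery are not among the listed data.

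For selenium and perhaps other laboratory outcomes, a pre-operative value gives some protection. Ventilation time and hospital stay have no such value, so adjustment would have to come from recorded risk factors. A difference in these outcomes, or in SOFA, could then reflect who received which technique and not the pump. Confounding could equally hide a real difference.

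This is not a complaint that the protocol omits a regression model; that could sit in an analysis plan that is not shown. An analysis plan can adjust only for what has been recorded, however, and the parameter list is fixed here.

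**Working it through.** **1. What the listed data can and cannot adjust for**

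| Item | Available before surgery according to the protocol? |
|---|---|
| Selenium | Yes, from the post-induction draw |
| Creatinine, albumin, bilirubin, troponin, CRP and other routine values | Possibly: they are to be related to selenium at matching time points, but they are described as daily measurements, so the timing of the first is unclear |
| SAPS | Listed without version or timing; if scored after surgery it may itself reflect the technique |
| Ventilation time, hospital stay | No baseline value can exist |
| Age, sex, ejection fraction, diabetes, urgency, surgical risk score | Not listed |

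Elective and urgent cases are both eligible, so urgency varies between patients, yet it is not a listed variable.

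**2. How large the effect could be**

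The only design figure in the protocol is 50 + 50 = 100. It gives no imbalance, SD or effect size, so everything below is assumed: 50 per group, a two-sided 5% normal test and no true difference between techniques. The false-positive rate is Φ(b/SE − 1.96) + Φ(−b/SE − 1.96), where b is the spurious difference.

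*One binary risk factor.* Its prevalence is p1 and p2 in the two groups, and it shifts the outcome by d residual SDs. Then b = (p1 − p2)d and SE² = [2 + p1(1 − p1)d² + p2(1 − p2)d²]/50.

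- 30% vs 20%, d = 0.5: b = 0.10 × 0.5 = 0.05; SE = √[(1.0525 + 1.0400)/50] = 0.205; rate about 5.7%.
- 40% vs 20%, d = 0.8: b = 0.20 × 0.8 = 0.16; SE = √[(1.1536 + 1.1024)/50] = 0.212; rate 11.7%.
- 45% vs 15%, d = 0.8: b = 0.30 × 0.8 = 0.24; SE = √[(1.1584 + 1.0816)/50] = 0.212; rate 20.5%.
- 45% vs 15%, d = 1.0: b = 0.30 × 1.0 = 0.30; SE = √[(1.2475 + 1.1275)/50] = 0.218; rate 28.0%.

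*One continuous risk factor.* The groups differ on it by Δ SD, and the outcome changes by r SD per SD of the factor. Then b = Δr, with SE = √(2/50) = 0.20. Each cell gives b and the false-positive rate.

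| Δ | r = 0.2 | r = 0.4 | r = 0.6 |
|---|---|---|---|
| 0.2 | 0.04; 5.5% | 0.08; 6.9% | 0.12; 9.2% |
| 0.5 | 0.10; 7.9% | 0.20; 17.0% | 0.30; 32.3% |
| 0.8 | 0.16; 12.6% | 0.32; 36.0% | 0.48; 67.0% |

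For scale, 50 per group detects (1.96 + 0.84) × 0.20 = 0.56 SD with 80% power. The spurious differences in the table run from 0.04 to 0.48 SD, so they range from negligible to nearly the size of difference that the study could reliably detect.

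**The case against.** The best defence is that the protocol already limits confounding. Emergencies, ischemic cardiomyopathy, valve disease and aneurysms are excluded, all patients have three-vessel disease, complete revascularization is intended, and a single surgeon removes differences between surgeons. The study also calls itself observational, and its leading variable, selenium, has a pre-operative value. All of this stands. It narrows the problem but does not balance age, diabetes, urgency or the remaining range of cardiac function.

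Three stronger readings are tempting, and the document does not support them.

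- A reader might infer that no pre-operative risk information is collected. Baseline selenium is collected, and creatinine and other laboratory values may be. The documentation form itself is not shown, so its full content is unknown; only the parameter list can be judged.
- A reader might infer that the comparison carries the surgeon's own selection. The protocol does not say who or what decides the technique, and one surgeon operating on everyone does not show selection by risk. What can be said is that the rule is unstated and that no randomisation is described.
- A reader might infer that the confounding can never be corrected. Recording is pseudonymized and only the analysis is anonymized, so chart data could still be added before the link is lost. Once it is lost, that may no longer be possible.

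It is also fair to say that the illustration rests wholly on assumptions and that its lower end is close to the nominal 5%.

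**Conclusion.** The point holds in a limited form. Technique is determined by an unstated, non-random process, and the listed parameters omit the main pre-operative risk factors. The group comparison of clinical course is therefore open to confounding that the listed data can correct only in part. This matters most for ventilation time and hospital stay, and less for laboratory outcomes that have a pre-operative value.

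The size cannot be determined from the protocol. Under the assumed scenarios the false-positive rate runs from 5.5% to 67.0%; moderate binary imbalances give about 12% to 28%. These figures show only that the problem may be trivial or serious, and that without recorded risk factors the study's own data could not show which. The missing suitability criterion is a design trade-off, not an error.

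**What to change.** Confirm that the documentation form holds the following items, or add them from the routine pre-operative chart before anonymization: age, sex, ejection fraction, a surgical risk score, diabetes, pre-operative creatinine, urgency (elective or urgent), the planned number of grafts and the reason for the chosen technique. The number of grafts should be the planned one, because the number performed is known only after surgery and may depend on the technique. Enrolment takes place no later than the evening before surgery, so these items can be recorded then.

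Compare clinical course between groups with adjustment for the pre-operative risk score. Adjust laboratory outcomes for their own pre-operative value as well. Describe the result as an association between technique and course.

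Restricting enrolment to patients judged suitable for both techniques is optional. It would make the groups more comparable, but it slows recruitment under the 24-month limit in the Study duration section and narrows the population to which the result applies. Recording suitability for both techniques and using it in a sensitivity analysis is the cheaper form.

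The cost is a few extra chart items per patient and some analysis work. Adjustment will not remove confounding by factors that remain unrecorded.

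### From the first post-operative morning on, samples are tied to the time of day and not to hours since surgery, which adds noise to early fast-changing markers and could bias the group comparison if elapsed time differs by technique

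*Protocol*

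**What the plan says.** The Methodology of study section of the protocol sets three kinds of draw. The first two are tied to events: "After induction of anaesthesia, within one hour after admission the patient to the intensive care unit". The rest are tied to the morning round: "every further morning on the intensive care unit or intermediate care unit (IMC), 10 ml blood will be drawn". The switch from one anchor to the other comes within a single sentence: "within one hour after admission the patient to the intensive care unit and every further morning". For the morning draws it gives no clock time, no number of hours since surgery and no window.

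The routine laboratory markers are daily values, to be "later correlated with the selenium concentration at the respective time points". The text after the parameter list adds that selenium, GPX, ADMA, IL-6 and IL-10 "from the 1.POD on will be used for possible long-term analyses of selenium course".

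The Statistic section plans tests for independent groups for the laboratory and clinical course, and Pearson and Spearman correlations. It mentions no term for elapsed time. The protocol calls the study observational and describes no randomisation. It plans 50 patients per technique, all operated on by one surgeon. It says that all data go on a documentation form, whose items are not shown.

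**The concern.** Two patients with the same post-operative course can reach the ICU at different hours of the day and still be sampled at the same hour next morning. Their POD 1 values then come from different points on the response, but they are analysed as one time point.

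Three consequences follow, in falling order of certainty:

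- **Noise.** For markers that move within hours, variation in elapsed time adds to the within-group spread and weakens both the group tests and the day-by-day correlations.
- **Shared time trend.** If selenium and a marker both change with hours since surgery, variation in those hours produces some correlation between them with no other link.
- **Group bias.** If mean elapsed time differs between on-pump and off-pump patients, for example through list order or operation length, the difference in timing appears as an effect of technique. Nothing in the design balances elapsed time between the groups.

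**Working it through.** **Inputs.** From the protocol: 50 patients per group, morning draws from POD 1 on, and tests for independent groups. The protocol gives no draw time, ICU arrival times, marker kinetics, standard deviations or significance level, and has no figure of its own to reproduce. Everything else below is assumed, for scale only:

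- draw at 06:00, with ICU arrival at 13:00 (early slot) or 19:00 (late slot); hours are counted from ICU arrival, as a stand-in for end of surgery
- log-linear decline with a half-life h of 6, 12, 24 or 72 h
- log-scale SD s of 0.5 to 0.8 at a fixed elapsed time
- two-sided 5% test

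**Step 1: spread within a nominal day.** Arrival at 13:00 gives 17 h to the draw, and arrival at 19:00 gives 11 h, a gap of 6 h. The ratio between two otherwise identical patients is 2^(6/h): 2.0 at h = 6, 1.41 at h = 12, 1.19 at h = 24 and 1.06 at h = 72.

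**Step 2: noise without any group imbalance.** If each group is half early and half late, elapsed time has an SD of 3 h. This adds a log-scale SD of t = 3·ln2/h, and the total SD is √(s² + t²).

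| h | t | total SD, s = 0.5 | total SD, s = 0.8 |
|---|---|---|---|
| 6 h | 0.347 | 0.608 (+22%) | 0.872 (+9%) |
| 12 h | 0.173 | 0.529 (+6%) | 0.819 (+2%) |
| 24 h | 0.087 | 0.508 (+1.5%) | 0.805 (+0.6%) |
| 72 h | 0.029 | 0.501 (+0.2%) | 0.801 (+0.1%) |

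**Step 3: bias if slot goes with technique.** Suppose 70% of one group and 40% of the other are in the early slot. The mean gap is g = (0.70 − 0.40) × 6 h = 1.8 h, and the spurious ratio is 2^(g/h). The log difference is b = g·ln2/h, and the test statistic is centred at b/(s·√(2/50)) = b/(0.2·s) instead of at zero. The false-positive rate is the chance of falling outside ±1.96, with s held fixed.

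| h | ratio | b | false-positive rate, s = 0.8 to 0.5 |
|---|---|---|---|
| 6 h | 1.23 | 0.208 | 26% to 55% |
| 12 h | 1.11 | 0.104 | 10% to 18% |
| 24 h | 1.05 | 0.052 | 6% to 8% |
| 72 h | 1.02 | 0.017 | about 5% (nominal) |

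If the slot mix is the same in both groups, g = 0, the ratio is 1 and only the noise of step 2 remains.

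**Step 4: later days.** The offset in hours is the same every day. Under a strictly log-linear decline the ratio would persist, although the absolute difference shrinks: at h = 12 it falls to 2^(−24/12) = 1/4 after one more day. Once a marker levels off, the ratio also goes to 1. Later days are therefore barely affected if markers have settled by then, which is itself an assumption.

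**The case against.** A morning draw is an ordinary choice in an observational study that rides on routine care. The protocol says nothing about theatre slots, which technique runs first, or operation length by technique, so the 70%/40% split is invented for scale. The half-lives are generic. None is specific to whole-blood selenium, the study's title variable, and if selenium moves slowly the effect on it is negligible. A covariate is also something that a statistical analysis plan may supply, and that plan is not shown. Clock times are normally in the chart, and the documentation form may already ask for them.

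Much of this stands, and it limits the point. Three stronger readings are not supported:

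- **That all post-operative samples float with the morning round.** The first is due "within one hour after admission the patient to the intensive care unit", so the change in selenium from induction to ICU arrival is untouched.
- **That the comparison of techniques is biased.** The protocol gives no evidence that elapsed time differs by technique. It only leaves this possible.
- **That night-time arrivals make the spread extreme.** Urgent cases are eligible, but emergency surgery is excluded and patients are enrolled no later than the evening before, so an arrival at 02:00 would be unusual.

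What survives is that the schedule is fixed in this protocol, that the analysis it states has no term for elapsed time, and that no later plan can adjust for hours that were not captured.

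**Conclusion.** The point holds as a cheap improvement, not as an error that undermines the study. It is certain from the text that morning samples have no anchor to surgery, so elapsed time can vary within a nominal day. Under the assumptions above, the added noise is material for a marker with a half-life near 6 h (SD up 9% to 22%), small at 12 h and trivial from 24 h on. Group bias is conditional on a mean timing difference by technique. With a difference of 1.8 h the spurious ratio runs from 1.23 (6 h) to 1.05 (24 h), and to about 1.02 at 72 h. The scope is POD 1, perhaps POD 2, and fast-changing markers. The induction and ICU-admission samples, the slow markers, and the late selenium course once values have settled are essentially unaffected.

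**What to change.** Keep the morning draw. Then:

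1. Record on the documentation form the clock time of end of surgery (or of ICU admission) and of every draw. Use one origin for both groups; end of bypass cannot serve, because it exists only in the on-pump group.
2. For POD 1, and POD 2 where the marker is still moving, compare the groups by regression with hours since end of surgery as a covariate, on the log scale for skewed markers. Use partial correlation given elapsed hours for the selenium-marker associations on those days.
3. Tabulate elapsed hours at the POD 1 draw by technique, so that readers can see whether timing differed.

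Do not replace this with a minimum-hours rule that moves short-interval draws to the next morning. With an 8 h cut-off, for example, the 17 h and 11 h patients both stay on POD 1 and their 6 h gap remains. A patient sampled 4 h after arrival would move to 28 h, so the POD 1 range would go from 4–17 h (13 h wide) to 11–28 h (17 h wide).

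The cost is two time fields and one extra model term. No extra blood is needed, and sampling and care do not change.

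### Morning samples stop when the patient leaves ICU/IMC, so later-day selenium means describe only those not yet discharged, and the group contrast on those days may be biased

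*Protocol*

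**What the plan says.** Under Methodology of study, two samples do not depend on how long the patient stays: "After induction of anaesthesia, within one hour after admission the patient to the intensive care unit". After that, "every further morning on the intensive care unit or intermediate care unit (IMC), 10 ml blood will be drawn", from the central venous line placed for the operation. No final sampling day is set and no sample is planned on the normal ward.

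The Risks section describes the daily draws as taken "every further day on the intensive care unit" and does not mention IMC.

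The later samples have four stated uses:

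- Under Determinated parameters, selenium, GPX, ADMA, IL-6 and IL-10 values "from the 1.POD on will be used for possible long-term analyses of selenium course".
- In the same section, the routine parameters are to be correlated with selenium at matching time points.
- Under Statistic, "Thereafter the mean and standard deviation of the recorded data will be calculated".
- Also under Statistic, OPCAB and conventional surgery are compared on laboratory and clinical course with tests for independent groups.

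The planned size is 50 patients per technique. The protocol calls the study observational and describes no randomisation.

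**The concern.** How long a patient is sampled is decided by how fast that patient recovers, and recovery is itself something the study measures (ventilation time, hospital stay, SOFA, clinical course by group). Patients who do well leave the unit and drop out of the later means.

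If lower selenium goes with greater severity, the mean among those remaining falls from day to day even when every patient's selenium is constant. The selenium course would then partly trace discharge rather than biology, and the correlations at later time points would come from the same shrinking set.

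The group contrast carries a further, conditional risk. If one technique leads to earlier discharge, its remaining patients are a more extreme selection, and a test among those still on the unit compares two differently selected subsets.

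The sampling rule is fixed in the protocol. A separate analysis plan could model the gaps but could not recover samples that were never drawn. The differing statements on IMC also leave it unclear when a patient leaves the sampled set.

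**Working it through.** The protocol gives no selenium SD, length of stay, discharge rate, alpha, power or effect size, so there is no stated figure to reproduce. What follows is an illustration.

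**From the protocol:** 50 CPB and 50 OPCAB patients; daily sampling conditional on unit stay.

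**Assumed:**
- Selenium has SD 1, no true group difference and no true time trend.
- Latent severity has correlation −a with selenium, a = 0.3 to 0.7.
- Severity has correlation r with remaining on the unit, r = 0.5 to 0.8.
- A share p remains on a given day.

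**Shift in the mean among those remaining.** With normal variables,

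shift = −a · r · φ(z)/p, where z is the (1 − p) normal quantile.

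φ(z)/p is 0.350 for p = 80%, 0.644 for 60%, 0.798 for 50%, 1.159 for 30% and 1.755 for 10%.

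| a, r | 80% | 60% | 50% | 30% |
|---|---|---|---|---|
| 0.3, 0.5 | −0.05 | −0.10 | −0.12 | −0.17 |
| 0.5, 0.8 | −0.14 | −0.26 | −0.32 | −0.46 |
| 0.7, 0.7 | −0.17 | −0.32 | −0.39 | −0.57 |

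Example: 0.7 × 0.7 × 1.159 = 0.57. Along a row, the mean falls as patients leave although nobody's selenium has changed. With only 10% remaining, the first two rows give −0.26 and −0.70.

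**Spurious group difference (CPB minus OPCAB).** This is a · r times the difference between the two φ(z)/p values.

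- Equal shares remaining: 0, with a rejection rate of 5.0%.
- 80% v 60%: 0.15 × (0.644 − 0.350) = 0.04 to 0.40 × 0.294 = 0.12.
- 50% v 30%: 0.15 × 0.361 = 0.05 to 0.40 × 0.361 = 0.14.
- 30% v 10%: 0.15 × 0.596 = 0.09 to 0.40 × 0.596 = 0.24.
- 60% v 30%, r = 0.7: 0.21 × 0.515 = 0.11 (a = 0.3), 0.35 × 0.515 = 0.18 (a = 0.5), 0.49 × 0.515 = 0.25 (a = 0.7).

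Here CPB is taken as the group with more patients remaining. The sign reverses if it is OPCAB.

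**Effect on a two-sided 5% test.** The standard error is √(1/n₁ + 1/n₂), keeping SD 1 among those remaining. For the 80/60, 50/30 and 30/10 splits, the rejection rate under no true difference is about 5.3% to 7.8%. For 60/30 (30 v 15 patients, standard error 0.316) it is 6.4%, 8.8% and 12.5% for a = 0.3, 0.5 and 0.7.

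**Loss of precision.** The detectable difference at 80% power is (1.96 + 0.84) × √(1/n₁ + 1/n₂).

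| Sampled | Detectable (SD) | Power for 0.5 SD |
|---|---|---|
| 50 v 50 | 0.56 | 70.5% |
| 40 v 40 | 0.63 | 61% |
| 25 v 25 | 0.79 | 42% |
| 25 v 15 | 0.91 | 33% |
| 15 v 5 | 1.45 | 16% |

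**Which samples are affected.** The post-induction and ICU-admission samples do not depend on length of stay. The first postoperative morning is affected only if patients have left ICU/IMC by then.

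**The case against.** A reader might infer that the two techniques do lead to different lengths of stay, and hence that the group comparison is biased. The protocol does not support that. It gives no stay or discharge figures by technique and lists a difference in clinical course as something to be tested. With equal discharge, the zero-effect group test is not biased. What stands is that unequal discharge is possible, since no randomisation is described.

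A reader might also infer that the study's main question is compromised. It is not: the effect of the pump on selenium can be read from the two samples that do not depend on length of stay.

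The sizes rest entirely on chosen correlations and shares. Even the largest 60/30 difference, 0.25 SD, is only 0.8 standard errors, and type I inflation is modest in most scenarios. This is fair, and it is why the numbers are an illustration. But the drift in the means and the loss of precision need no difference between techniques.

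The text is also loose. The long-term analyses are called only possible, no per-day group test is spelled out, and incomplete repeated measures are commonly handled in an analysis plan. That lowers the weight of the point without removing it, because the protocol itself fixes the sampling rule and names the means, the correlations and the type of test.

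Finally, the Risks sentence may be a shortened restatement of the schedule. That is likely, so the IMC mismatch is minor.

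**Conclusion.** The point holds in conditional form. Followed as written, the protocol yields later-day means, correlations and group tests that apply only to patients still on the unit. If severity relates to both selenium and stay, the means shift: by about 0.05 to 0.57 SD with 80% to 30% remaining, under the assumed correlations. Bias in the CPB versus OPCAB contrast on those days additionally needs discharge to differ by technique, which is possible but nowhere stated. It is about 0 with equal discharge and 0.04 to 0.25 SD in the unequal scenarios shown. Falling numbers cost precision in either case. The direct contrast at induction and ICU admission is untouched. The change should be made, because it is cheap and a named use of the data could otherwise mislead.

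**What to change.** - Base the direct CPB versus OPCAB tests on the post-induction and ICU-admission samples. Add the first postoperative morning only if virtually all patients are still sampled then.
- Analyse later days with a likelihood-based mixed model for repeated measures that uses all samples of all patients, with technique, time and technique-by-time, in place of independent-group tests among those remaining.
- Report the number sampled per day and group beside every later-day summary.
- Label later-day results as conditional on missing-at-random.
- Reconcile Methodology of study with Risks on whether IMC days are sampled.

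The cost is a few sentences of statistical text and one corrected sentence, with no extra blood draws. The small downside is that the mixed model removes the bias only if discharge depends on what was already observed, given the model. The calculation above does not test that, so later-day results stay more tentative than the two early samples.
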